### Data Collection and Management

#### Overview

Data for this study are collected from electronic medical records and patient-reported questionnaires during study visits. Clinical and demographic information, including age, sex, educational level, BMI, diabetes duration, comorbidities, complications, and current pharmacological treatment, is obtained from the eCAP (electronic medical record) software and supplemented by medical interviews. Laboratory variables, including C-peptide, GADAb, HbA_1c_, and estimated glomerular filtration rate, are extracted from recent laboratory reports or requested when unavailable. CGM data, including metrics such as time in range, hypoglycemia episodes, and glucose variability, are downloaded directly from the devices used by participants throughout the study. Patient-reported outcomes, including quality of life, treatment satisfaction, medication adherence, and physical activity, are assessed using validated questionnaires. All study variables and corresponding time points are summarized in Table 1. In addition, detailed information on the study variables, including their definitions and data sources, is provided in Multimedia Appendix 2.

**Table 1. T1:** Study timeline, variables, and procedures.

Data collected	Evaluation time point			
	Preselection	Visit 0—inclusion	Visit 1—intervention (2 weeks)	Visit 2—final follow-up (6 months)
Inclusion and exclusion criteria	✓	✓		
Sociodemographic data^a^		✓		
Anthropometric data^b^		✓		✓
Clinical data^c^		✓		✓
CGM^d^ data			✓	✓
Laboratory data^e^		✓		✓
Smoking status		✓		
Pharmacological treatment^f^		✓		✓
Severe hypoglycemia^g^		✓		✓
Questionnaires^h^		✓		✓

a Age, gender, primary care center, current occupational status, level of education, number of children, date of menopause, and whether the participant is the sole caregiver of another person.

b Weight, height, BMI, and abdominal circumference.

c Arterial hypertension, dyslipidemia, micro- and macrovascular complications, heart failure, and renal disease of any etiology (estimated glomerular filtration rate <60 mL per minute per 1.73 m2).

d CGM: continuous glucose monitoring.

e Inclusion visit: hemoglobin A_1c_ (HbA_1c_), glutamic acid decarboxylase autoantibody, glycemia, and C-peptide; final visit: HbA_1c_.

f Prescription and dosage of diabetes drugs.

g Inclusion visit: last 12 months; final visit: 6 months of study.

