### Sample Size and Statistical Analysis

At the time of the study planning, data from the Lleida health care region had identified 1388 people with T2DM treated with MDI. On the basis of prior clinical experience, approximately 25% of these individuals may have sufficient residual β cell function to discontinue prandial insulin. To estimate this proportion with a 95% CI and a margin of error of –5% to +5%, a sample size of 239 participants was estimated.

The study population will be characterized at baseline with respect to age, BMI, duration of diabetes, presence of chronic diabetes-related complications (microvascular and macrovascular), and cardiovascular risk factors. In addition, in-depth phenotyping will be performed using the homeostatic model assessment of β cell function and homeostatic model assessment of insulin resistance indexes [27] and GADAb measurements.

For the primary outcome, the proportion of participants who discontinue prandial insulin after the application of the diagnostic algorithm and sustain this change over a 6-month follow-up period will be calculated, along with its corresponding 95% CI.

Secondary outcomes will include measures of glycemic control, patient-reported outcomes, and safety outcomes. Glycemic control will be assessed using HbA_1c_ and CGM-derived metrics, including time in range (70‐180 mg/dL), time below range, time above range, mean glucose, and glycemic variability indexes. Patient-reported outcomes will include validated scores for treatment satisfaction, adherence, and quality of life analyzed according to each instrument’s scoring manual. Safety outcomes will include the incidence of severe hypoglycemia.

To evaluate changes over time (eg, from baseline to follow-up visits), paired 2-tailed *t* tests or Wilcoxon signed-rank tests will be used depending on data distribution. Between-group comparisons (eg, discontinuation vs continuation of prandial insulin) will be conducted using Student *t* tests or Mann-Whitney *U* tests as appropriate, as well as using linear mixed-effects models to account for within-subject correlation.

For categorical secondary outcomes, including severe hypoglycemia, comparisons between groups will be performed using chi-square or Fisher exact tests as appropriate. For outcomes measured repeatedly across follow-up visits, analyses will be conducted using linear mixed-effects models.

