CGM variables will also be examined as potential predictors of pancreatic reserve and insulin resistance. Depending on whether outcomes are continuous or categorical, linear or logistic regression models will be applied. Results will be expressed as regression coefficients or odds ratios with corresponding 95% CIs.

Loss to follow-up will be quantified and reported as the proportion of participants without outcome data at each follow-up time point. When available, reasons for loss to follow-up will be documented. Baseline characteristics of participants with complete follow-up and those lost to follow-up will be compared to assess potential differential attrition. A complete-case analysis will be used as the primary analytical approach when the proportion of missing data is low, and missingness will be considered compatible with a missing completely at random mechanism. To account for potentially informative missingness, multiple imputation by chained equations will be performed under a missing-at-random assumption, including all variables used in the main analyses and auxiliary variables related to missingness.

All statistical analyses will be performed using the R software (version 4.1.2; R Foundation for Statistical Computing), with a 2-sided *P* value of <.05 considered statistically significant.

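### A general complete-case rule is applied to a primary outcome that can often be established without Visit 2, and missing-at-random imputation is offered as the remedy for informative loss, which it does not cover

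*Protocol article*

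**What the plan says.** All references are to the protocol article.

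- **Primary outcome.** Study Outcomes defines success as having stopped prandial insulin after the algorithm and being without it at the 6-month visit. Sample Size and Statistical Analysis counts those who stop and "sustain this change over a 6-month follow-up period", and reports the proportion with a 95% CI.
- **Who stays on prandial insulin.** Intervention Algorithm leaves treatment unchanged when C-peptide is below 0.3 nmol/L, or is 0.3 to 0.7 nmol/L with positive GADAb. In the other groups stopping is considered. Study Procedures and Timeline places the decision at Visit 1.
- **Treatment data.** Under Data Collection and Management, "current pharmacological treatment, is obtained from the eCAP" record, supplemented by interview. Table 1 schedules it at Visits 0 and 2.
- **Missing data.** Loss means having no outcome data. "A complete-case analysis will be used as the primary analytical approach when the proportion of missing data is low", with missingness regarded as compatible with missing completely at random (MCAR). The next sentence reads: "To account for potentially informative missingness, multiple imputation by chained equations will be performed under a missing-at-random assumption".

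**The concern.** There are two problems.

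**The rule does not fit the outcome.** Complete-case analysis is a generic choice for variables that exist only if the visit takes place, such as a questionnaire score. Month-6 prandial insulin status is different. Participants whom the algorithm leaves on prandial insulin will, as a rule, be non-successes. For those who stopped, a later prescription is in a record the study already uses. Nothing in the article says that this information assigns status when Visit 2 is missed.

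**The remedy does not match its stated purpose.** Missingness is informative, in the usual sense, when it depends on the unseen value. Missing-at-random (MAR) assumes that this dependence is absent once the observed variables are taken into account. Participants who went back to prandial insulin might be less likely to return. If so, MAR imputation does not correct for it, and the article names no analysis under a not-at-random assumption.

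What is at stake is the study's main result: one proportion, to be estimated within 5 points.

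**Working it through.** **1. The plan's own figure.** Inputs from Sample Size and Statistical Analysis: "approximately 25% of these individuals may have sufficient residual β cell function to discontinue prandial insulin" (p = 0.25), a 95% CI with margin d = 0.05, and a source population that "had identified 1388 people with T2DM treated with MDI".

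- Without finite population correction: n0 = 1.96² × 0.25 × 0.75 / 0.05² = 288.1, so 289.
- With correction: n = 288.1 / (1 + 287.1/1388) = 238.7, so 239.

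This matches "a sample size of 239 participants was estimated". It contains no allowance for loss. With the same correction, the half-width is 5.0 points at n = 239. At 5, 10, 15 and 20% loss (n = 227, 215, 203, 191) it is 5.15, 5.32, 5.50 and 5.70. The loss of precision is small, so bias is the main issue.

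**2. Complete-case estimate under unequal loss.** The article gives no loss rates, so all rates below are assumptions. The true value is set at 25%. With loss a among sustained stoppers and b among everyone else:

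estimate = 0.25(1−a) / [0.25(1−a) + 0.75(1−b)]

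| a | b | Overall loss | Calculation | Complete-case |
|---|---|---|---|---|
| 10% | 10% | 10% | 0.225 / 0.900 | 25.0% |
| 5% | 20% | 16.25% | 0.2375 / 0.8375 | 28.4% |
| 20% | 5% | 8.75% | 0.200 / 0.9125 | 21.9% |

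The error is +3.4 or −3.1 points, and zero when loss is equal.

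**3. What MAR imputation does.** Assume 40% stop at Visit 1: 60% never stop, 15% stop and resume, 25% stop and sustain. Let the imputation use Visit 1 stop/continue status, so that never-stoppers are imputed as non-successes and lost stoppers receive the rate seen in observed stoppers.

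*Loss depends on the outcome* (30% of resumers, 5% elsewhere). Observed fractions are 0.57, 0.105 and 0.2375, in total 0.9125 (8.75% lost).
- Complete-case: 0.2375 / 0.9125 = 26.0%.
- MAR imputation: 0.40 × 0.2375 / (0.105 + 0.2375) = 27.7%.

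Here imputation is further from 25% than complete-case analysis.

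*Loss depends only on Visit 1 status* (20% of never-stoppers, 5% of stoppers). Observed fractions are 0.48, 0.1425 and 0.2375, in total 0.86 (14% lost).
- Complete-case: 0.2375 / 0.86 = 27.6%.
- MAR imputation: 0.40 × 0.2375 / 0.38 = 25.0%.

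Here imputation works, provided that Visit 1 status is in the model.

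**4. Bounds with no assumption about mechanism.** If 25% is observed in completers, counting all lost as failures and then as successes gives:
- 10% loss: 0.25 × 0.90 = 22.5%, to 22.5 + 10 = 32.5%.
- 20% loss: 0.25 × 0.80 = 20.0%, to 20.0 + 20 = 40.0%.

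The first range is as wide as the whole planned interval; the second is twice as wide.

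**5. With status resolved.** If every missed Visit 2 were correctly resolved from the Visit 1 decision or the record, the denominator stays at 239, the half-width at 5.0 points, and the estimate is 25% in every scenario above.

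**The case against.** A reader might infer that the plan drops known failures and so inflates the result. The article does not support that.

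- **Loss is defined by absent outcome data, not by a missed visit.** A participant whose month-6 treatment is in eCAP could count as a complete case. The text is silent on this, not contrary to it.
- **A Visit 1 continuer is not a certain non-success.** Clinicians only consider stopping in the eligible groups, the Limitations describe flexible use of the algorithm, and support contacts follow Visit 1. A later stop is not clearly excluded.
- **The direction is open.** Step 2 shows error both ways, and none under equal loss. If 60 of 239 truly succeed (25.1%) and every loss falls among those kept on prandial insulin, complete-case gives 60/215 = 27.9% or 60/191 = 31.4%. That is an extreme case, and imputation using Visit 1 status would correct it.
- **Imputation is not worded as a fallback.** It will be performed without a stated condition, and it includes auxiliary variables related to missingness.
- **Sustained status need not require dated prescriptions.** Study Outcomes defines it as status at the final visit, which Table 1 covers.
- **A threshold for low missingness** is detail that the full protocol or analysis plan may hold, so its absence here is not counted.

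All of this stands and limits the point. It does not remedy the pairing of informative loss with a MAR method. If informative was meant only as not MCAR, the method is suitable and the word is wrong. Nor does it supply the rule for a missed Visit 2.

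**Conclusion.** The point holds in a limited form. A complete-case rule resting on MCAR is a poor choice for a binary outcome that can often be established without Visit 2. MAR imputation is also described as dealing with something that it does not deal with when loss depends on the unseen outcome.

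As written, the plan may drop participants whose status is known, and the headline proportion could move either way. The size is about 3 points against a 5-point margin, if loss is 5% in one outcome group and 20% in the other. In the resumer scenario the error is 1.0 point for complete-case and 2.7 points for MAR imputation. These figures rest on assumed loss rates and an assumed 40% stopping at Visit 1, and they do not predict what the study will show. The point is worth acting on because the better method is cheap. It applies to the primary outcome only: HbA1c, CGM metrics and questionnaires cannot be recovered from prescriptions in this way.

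**What to change.** For the primary outcome only:

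1. Keep all enrolled participants in the denominator.
2. When Visit 2 is missed, assign status from the Visit 1 decision together with dated eCAP prandial insulin prescriptions to month 6. Check the record for any later stop among Visit 1 continuers. Table 1 does not schedule treatment data at Visit 1, so state where that decision is recorded.
3. For those still unknown, use chained-equations imputation with Visit 1 stop/continue status, C-peptide and GADAb in the model.
4. Add best/worst bounds or delta-adjusted imputation as the not-at-random sensitivity analysis, including the case where every unknown counts as not sustained. Complete-case results can be reported alongside.
5. Reword the missing-data paragraph so that MAR imputation is not said to account for informative missingness.

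The cost is one query in a system the study already uses and a little more analysis. The drawback is that a prescription may not equal actual use, which should be stated with the result. The Results section says that formal analysis begins only after follow-up ends. If it has not begun, all this can be fixed before any estimate is seen.

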### Ethical Considerations

#### Overview

This study will be conducted in accordance with the Declaration of Helsinki and the principles of good clinical practice. The study protocol received approval from the ethics committee of Institut Universitari d’Investigació en Atenció Primària Jordi Gol i Gurina, the research institute for primary care in Catalonia. The approved protocol is registered under reference 23/193-EOm. Participants did not receive any financial or material compensation for taking part in the study.

The trial is registered at ClinicalTrials.gov with the identifier NCT06148376.

#### Informed Consent

All participants received verbal and written information about the study and provided signed informed consent before enrollment. When participants had limited capacity to consent, their legal representatives may provide authorization.

#### Data Protection and Confidentiality

All personal data will be pseudonymized and processed in compliance with the General Data Protection Regulation (2016/679) and Spanish Organic Law 3/2018 on the Protection of Personal Data and Guarantee of Digital Rights. Individual patient information will be encrypted to ensure anonymity. Only authorized researchers and study monitors will have access to the data.

### Publication Commitment

The results of the study will be disseminated regardless of the outcome and will be submitted for peer-reviewed publication. Participant confidentiality will be maintained in all presentations and publications.

## Results

Recruitment for the study began in January 2024 and was completed on March 31, 2025.

As of August 31, 2025, the study is in its final follow-up phase, scheduled to conclude on September 30, 2025. Formal data analysis will begin after completion of follow-up and final data collection.

## Discussion

### Expected Findings

According to data from the Catalan Agency for Health Quality and Assessment and the eCAP electronic medical record system, the Lleida health care region has approximately 27,769 individuals diagnosed with T2DM, representing 8.95% of the adult population. Among these patients, 5% are currently treated with MDI.

This study aims to improve the available evidence in precision medicine for T2DM, specifically targeting patients treated with MDI. Using the simple precision medicine algorithm (Figure 1) proposed in this study based on assessment of β cell function (C-peptide) and autoimmunity (GADAb), we will evaluate whether prandial insulin can be safely removed or replaced by another treatment in real-world clinical practice.

The study’s main outcome is the proportion of patients in whom prandial insulin is successfully discontinued and remains unnecessary at 6 months. Secondary outcomes include clinical measures such as HbA_1c_ levels; CGM-derived metrics related to insulin resistance and pancreatic function; incidence of severe hypoglycemia; and several patient-reported outcomes—including quality of life, treatment satisfaction, medication adherence, and physical activity. Among patients who continue prandial insulin and CGM, the study also examines the added value of CGM use on both metabolic control and patient experience.

The algorithm is implemented by a multidisciplinary research team—including general practitioners, endocrinologists, and nurses—who integrate biomarker results with patient-specific clinical characteristics to guide medical decision-making. The strategy proposed by this study is intended for inclusion in clinical practice. If successful, this approach could be adopted by health care professionals managing T2DM to achieve simpler, safer, and more effective treatment strategies, particularly those that offer cardiovascular, renal, and weight management benefits.

This personalized strategy aligns with a broader innovation trend in diabetes care. Similar to the study by Dennis et al [28], which developed and validated a predictive model to individualize glucose-lowering therapies in T2DM, our project aims to move beyond conventional treatment algorithms by incorporating patient-specific pathophysiological characteristics.

Adopting a simple, precision-based approach to T2DM represents both a challenge and an opportunity. It can foster improved coordination between primary and specialized diabetes care teams and enhance understanding of diabetes heterogeneity. This study exemplifies how precision strategies can be tested and implemented in standard care settings. By enabling more individualized treatment decisions, the intervention may reduce overtreatment, minimize hypoglycemia, enhance quality of life, empower patients, and strengthen the use of digital health tools and telemedicine in routine care.

### Limitations

This study has several limitations. First, as with many observational studies involving voluntary participation, there is potential selection bias. Individuals who choose to participate may differ systematically from those who do not, for example, by being more motivated, having greater health literacy, or exhibiting more stable diabetes management. Such characteristics could affect adherence, clinical outcomes, and openness to treatment simplification, thereby potentially limiting the generalizability of the findings [21].

Second, although the study includes all persons with a diagnosis of T2DM treated with MDI within the participating centers, recruitment depended on the initiative of local primary care teams, which may introduce variability in enrollment rates and patient selection. Third, the intervention algorithm offers flexibility in its clinical application, potentially leading to deviations from the proposed protocol. However, given the pragmatic nature of the study, this flexibility is considered necessary to ensure patient safety and adapt the intervention to the heterogeneous clinical profiles of T2DM, a condition influenced by multiple factors affecting treatment response. Lastly, the duration of diabetes may affect the reliability of autoantibody testing. In long-standing cases, GADAb titers may decline over time, leading to false-negative results. Although longitudinal data are limited, up to 40% of GADAb-positive patients may become seronegative 10 years after diagnosis [29]. Despite this, GADAb was selected over other autoantibodies due to its higher prevalence and persistence in patients with LADA [5].

In summary, these limitations—including the use of convenience-based recruitment, potential selection bias, variability in recruitment across centers, and the pragmatic flexibility of the intervention algorithm—should be considered when interpreting the findings. These factors may limit causal inference and applicability, but they are consistent with the study’s feasibility-focused, real-world nature.

### Conclusions

More accurate phenotyping of persons with T2DM on MDI may improve diagnostic accuracy and enable treatment optimization by identifying candidates for prandial insulin withdrawal or for the introduction of agents with better safety profiles and added cardiovascular benefits [30].

Simplifying therapeutic strategies in T2DM management can be effective provided that personalized care is prioritized, patient safety is preserved, and glycemic control is maintained.

Furthermore, implementing CGM represents both a challenge and an opportunity to enhance diabetes care across primary care and endocrinology services. Strengthening collaboration across care levels and promoting the use of digital health tools may empower patients and improve the management of this highly prevalent and impactful chronic disease.
